### Secondary outcome measures

Pain is assessed at all time points using the revised Venous Clinical Severity Score (VCSS). This revised VCSS is a valid and reliable instrument to measure severity of venous disease, pain specific to chronic venous disease of the legs, and response to treatment over time that can be compared across studies [35]. Quality of life is measured at weeks 0 and 12 using the Venous Insufficiency Epidemiological and Economic Study-Quality of Life/Symptoms **(**VEINES-QOL/Sym) questionnaire, based on the Short Form – 36 (SF-36) questionnaire [36]. VEINES-QOL/Sym is a standardized, 26-item, patient-reported questionnaire to assess the severity and frequency of venous insufficiency symptoms.

CVLU recurrence will be assessed in two subgroups derived from the EPA + DHA group. Unblinding will occur at week 12. If participants in the EPA + DHA group have healed CVLUs by week 12, they will be asked to consider participating in a continuing study to determine the preliminary efficacy of continuing EPA + DHA therapy in preventing ulcer recurrence. If participants agree to participate, they will be randomly assigned 1:1 to either of two subgroups: subgroup 1 will continue EPA + DHA therapy for three more months, while subgroup 2 will receive placebo therapy. The PI and participants will be blinded to treatment. Three months later, participants in the subgroups will return for a final study visit (visit 5).

### Covariates

To address potential confound of variables that may impact inflammation or wound healing [37], we are collecting data on age, sex, tobacco use, comorbidities, perceived stress, and prescribed/over-the-counter medications. We are also collecting data on dietary intake of nutrients that may affect healing (e.g., vitamin C and protein) using a food frequency questionnaire [38]. All instruments being used to measure tobacco use, perceived stress, and dietary intake have been well vetted so data can be compared across studies. We are also determining if wound debridement or adjunct therapies were used between study visits and noting the type of dressing under compression bandaging.

### Statistical analysis

Congruent with the RCT design of the study, we will conduct an intent-to-treat analysis. We will first use descriptive statistics to check data distribution, identify outliers, guide appropriate data transformation if needed, and summarize sample characteristics. Two-sample *t* tests and Chi-square statistics will be used to check the balance of baseline measures between two study arms. Mixed-effects linear modeling for repeated measures will be used to test the intervention effect on each outcome measure (PMN activation, lipid mediators, inflammatory cytokines, inflammatory cytokine gene expression, percent reduction in wound area, and pain and QoL). In each model, we will include fixed-effects of treatment (EPA + DHA vs. control), time, and treatment by time interaction, adjusting for possible covariates (e.g., lipid-lowering medications) and data dependancy from repeated measures. From the mixed-effects modeling, we will derive the between-group contrast (EPA + DHA vs. control) estimates of change from baseline in outcome variable at each follow-up time point. Multiple comparison adjustment (e.g., Bonferroni adjustment) will be applied to these between-group contrasts to avoid inflated type I error. Logistic regression modeling will be used to analyze wound recurrence. Again, we will estimate between-group difference in the risks of wound recurrence, adjusting for potential covariates and multiple comparison. Lastly, we will use longitudinal mediation modeling [39] to test hypothesized mediating pathways. A significant mediation pathway is indicated if both paths from X (e.g., treatment) to M (mediator, e.g., pro-inflammatory cytokine) and from M to Y (e.g., PMN activation) are statistically significant. Adequate model fit of a mediation model will be indicated with a non-significant Chi-square statistic, comparative fit index, and Tucker & Lewis Index ≥ 0.9, and a root mean square error of appromixation of ≤ 0.08 [40]. The effect of biological sex and its interaction with treatment will also be examined in the regression models. Missing Data. We expect missing data due to non-adherence, loss of follow-up, or lack of data due to healed wounds. We will carefully examine the extent and pattern of missing data. We will use an indicator variable to flag missing data due to healed wounds and incoporate the variable in the missing pattern analysis. Mixed-effects modeling allows for missing at random [41]. If missing completely at random (MCAR) exists, multiple imputation will be used in order to use the optimal amount of information in our analysis. For missing not at random, pattern-mixture modeling will be used [42]. We will also conduct sensitivity analysis to examine the robustness of study findings from different methods. The trial is considered “minimal risk” by the local IRB and therefore no interim analysis or formal plans for stopping the trial are planned. In terms of data and safety monitoring, a Safety Officer (SO) has been selected and approved by the funding agency in consultations with the PI. The SO has no financial, scientific, or other conflict of interest with the trial. The SO meets with the PI twice annually to review study progress, data quality, and participants’ safety.

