## Background

Chronic venous leg ulcers (CVLUs) are open skin lesions of the lower legs arising in areas affected by venous hypertension that have been present for at least 6 weeks [1]. These common conditions affect 1% of the adult population and 3.6% of people older than 65 years, and the incidence of CVLUs is rising because they mainly occur in older adults with comorbidities, a growing population [2]. These recurring, disabling wounds cause substantial infirmity [3]. Quality of life (QoL) declines due to related pain, reduced mobility, and protracted treatments that cost payers in the United States alone up to $15 billion per year [4].

Multilayer compression bandaging is the gold standard therapy for CVLUs to reduce venous hypertension in the lower extremities implicated in the pathobiology of CVLUs [5]. However, even with compression therapy, the median time to complete healing of uncomplicated CVLUs is reported to be 12 weeks; older (> 6 months) and larger ulcers (> 20 cm^2^) require significantly more time to heal [6]. Other data indicate that nearly 60% of CVLUs remain unhealed after 12 weeks of compression therapy and usually recur [7, 8]. Thus, new therapies to augment compression bandaging and other standard topical therapies are needed to improve CVLU outcomes and help prevent recurrence [9].

The pathobiology of CVLUs also involves high numbers of activated polymorphonuclear leukocytes (PMNs) in venous circulation and ulcer microenvironments that promote unremitting inflammation and delay healing [10–12]. Although PMNs (e.g., neutrophils) are essential for a short time in the first stage of wound healing to fight off potential pathogens [13], sustained high levels of PMNs typically found in CVLU microenvironments are detrimental to healing. Sustained high levels of PMNs lead to excessive amounts of PMN-derived proteases such as human neutrophil elastase that ultimately destroy newly formed tissue and degrade growth factors, receptors, and the extracellular matrix that are essential for healing [10, 11, 14, 15]. Excessive, prolonged levels of PMNs keep ulcers “trapped” in a chronic inflammatory state. Further, high levels of activated PMNs in venous circulation are involved in CVLU onset [9, 16, 17]. As such, reducing excessive PMN activation systemically and locally is expected to resolve inflammation, advance ulcers through subsequent stages of healing, and deter recurrence.

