### Sample size

Sample size was determined to have sufficient power to detect intervention effect on wound healing, the optimal outcome of the study. Using mixed-effects linear modeling for repeated measures, a total of 248 participants (124 per group) are needed to have 80% power to detect an effect size of 0.4 for between-group comparisons in percent wound area reduction. We assumed (1) a first-order autoregressive covariance structure among the three post-intervention repeated measures, (2) a within-subject correlation of 0.7, and (3) an attrition rate of 20% in the sample size calculation. These assumptions are reasonable based on data from our pilot study [25]. The effect size of 0.4 is corresponding to an average of 16% between-group difference in percent wound area reduction with a common standard deviation of 0.4. Our power analysis also applied Bonferroni method to adjust for three comparisons of primary interest (4-week vs. baseline, 8-week vs. baseline, and 12-week vs. baseline). We used the same approach to conduct power analysis for other outcomes. Our sample size will have over 90% power to detect intervention effects on levels of lipid mediators and inflammatory cytokines and PMN activation, which had medium to large effect sizes based on our pilot study [25, 29]. A two-sided significance level of 0.05 was used for all power analyses. Based on OSU CWC data, we will be able to recruit the required number of people (*n* = 248) in the 53-month recruitment period, averaging 4–5 per month.

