### Randomization and intervention

After written informed consent is obtained, patients eligible for the study are randomly assigned to either the treatment group or the placebo group by the project manager using the stratified permuted block randomization scheme generated by the study statistician. Precisely, we divide participants in each age stratum (55–69 vs. 70+ years) into permuted blocks of varying block sizes (4 or 8 people/block). Those in each block will be randomly allocated with a ratio of 1:1 to either of the two study arms. Those in each arm will consume softgels of allocated therapy (EPA + DHA or placebo) daily for 12 weeks. Stratified permuted block randomization ensures balanced randomization across age groups and over time. The varied block sizes were chosen to prevent predictability in treatment allocation. The study participants, clinicians, and researchers are blinded as to treatment.

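### The planned contrasts are changes from baseline with no stated baseline adjustment, and the models do not fix the age stratum or, for healing, ulcer area and duration: precision is given up

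*Protocol article*

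**What the plan says.** All places are in the protocol article.

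- **Statistical analysis.** Each outcome gets a mixed-effects linear model with treatment, time and their interaction, "adjusting for possible covariates (e.g., lipid-lowering medications) and data dependancy from repeated measures". The treatment effect is the between-group contrast in "estimates of change from baseline in outcome variable at each follow-up time point". No baseline covariate or equal-baseline constraint is stated. Lipid-lowering drugs are the only covariate named in that model statement.
- **Randomization and intervention.** Allocation is stratified by age: "we divide participants in each age stratum (55–69 vs. 70+ years) into permuted blocks of varying block sizes (4 or 8 people/block". The fixed effects listed for the models do not include this stratum.
- **Background.** On prognosis under compression: "older (> 6 months) and larger ulcers (> 20 cm^2^) require significantly more time to heal".
- **Eligibility criteria.** Target wounds of 2–60 cm² and of 4 weeks to 12 months' duration are admitted, so both cut-points in the Background fall inside the enrolled range.
- **Covariates.** "we are collecting data on age, sex, tobacco use, comorbidities, perceived stress, and prescribed/over-the-counter medications"; diet, debridement, adjunct therapies and dressing type follow. Age is listed. Ulcer area and ulcer duration are not.
- **Aim 3** (Abstract and Background) undertakes to adjust the wound-area comparison for influences on healing, without listing them.

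**The concern.** Two separate sources of precision are left unused.

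First, in a model with free week-0 means in each arm, the change-from-baseline contrast with complete data is the difference in mean change. Randomisation makes the true week-0 means equal. Subtracting the whole observed baseline, rather than its regression-weighted share, therefore adds noise whenever the correlation with baseline is below 1. This touches PMN activation, lipid mediators, cytokines, gene expression, pain and QoL.

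Second, an analysis that ignores a stratification factor tends to overstate the standard error. One that ignores strong prognostic factors leaves their variance, and any chance imbalance in them, in the comparison. The article itself identifies ulcer size and age as prognostic for healing, stratifies on neither, and lists neither as a covariate.

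At stake are wider confidence intervals and lower power than the same participants could give. An open covariate set also leaves room for later choice.

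**Working it through.** **1. The plan's own sample size.** Inputs from the Sample size section: "a total of 248 participants (124 per group) are needed to have 80% power to detect an effect size of 0.4"; "an average of 16% between-group difference in percent wound area reduction with a common standard deviation of 0.4", so d = 0.16/0.40 = 0.4; AR(1) with correlation 0.7 among the three post-intervention measures; Bonferroni for three comparisons, so two-sided α = 0.05/3 = 0.0167; 20% attrition.

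Variance of the mean of three AR(1) measures, per unit variance: (3 + 2(0.7 + 0.7 + 0.49))/9 = 0.7533. With d = 0.4, α = 0.0167 and 80% power this gives 99 per arm. Then 99/0.80 gives 124 per arm, 248 in total, which matches. (One visit at unadjusted α = 0.05 also gives 99.) With 124 × 0.8 = 99.2 evaluable per arm, power for the three-visit average is 80.3%. No covariate gain was needed, so N does not depend on this point.

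**2. Change score against baseline adjustment.** Per unit outcome variance, with equal variances at baseline and follow-up:
- change from baseline: 2(1 − r)
- baseline-adjusted: 1 − r²
- ratio, adjusted to change: (1 + r)/2

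The article gives no baseline-to-follow-up correlation, so two assumptions bracket the result.

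| Assumption | Visit | r | Change | Adjusted | Ratio |
|---|---|---|---|---|---|
| Constant 0.7 | any | 0.7 | 0.600 | 0.510 | 0.85 |
| AR(1) 0.7 extended to week 0 | week 4 | 0.7 | 0.600 | 0.510 | 0.85 |
| same | week 8 | 0.49 | 1.020 | 0.760 | 0.745 |
| same | week 12 | 0.343 | 1.314 | 0.882 | 0.671 |

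The variance reduction is 15% at every visit under the first assumption, and 15%, 25.5% and 33% under the second. For an assumed 0.4 SD effect, α = 0.0167 and 99.2 per arm, week-12 power is 52.5% (change) against 72.7% (adjusted) under extended AR(1), and 89.3% against 94.0% with r = 0.7 throughout.

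**3. Age stratum alone.** Target recruitment is 168 and 80, so p = 80/248 = 0.323 and p(1 − p) = 0.2185. For a between-stratum difference of δ SD, R² = 0.2185δ²/(1 + 0.2185δ²). An assumed δ of 0.2 gives about 0.009, and 0.5 gives about 0.05.

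**4. Ulcer area and duration in the wound model.** Residual variance is multiplied by (1 − R²). The article gives no R², so a range is assumed:

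| R² | Power, three-visit average | N for 80% power |
|---|---|---|
| 0 | 80.3% | 248 |
| 0.02 | 81.2% | 244 |
| 0.05 | 82.5% | 236 |
| 0.10 | 84.8% | 224 |
| 0.20 | 89.2% | 198 |
| 0.30 | 93.1% | 176 |

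**The case against.** The strongest reply is that silence is being read as exclusion. The covariate set is open-ended, Aim 3 commits to adjusting for influences on healing, and the Covariates section lists age. A full covariate list is commonly left to an analysis plan, which is not shown. This stands as far as it goes: a reader might infer that the plan omits these terms deliberately, and the text does not support that. What remains is narrower. The article does state a contrast and a set of fixed effects, and its own list of covariates does not contain the two factors that its Background calls prognostic.

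A contrast in change does not by itself settle the estimator: with the baseline value as a covariate, the effect on change equals the effect on the follow-up value. That is correct, and it is why the fix is easy. But the stated terms, taken as written, give free week-0 means.

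The change-score argument does not reach percent wound area reduction, the outcome on which the trial was sized. It is already expressed relative to week 0, so there the question is only about covariates. This stands.

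The sizes rest on assumptions. The AR(1) structure is stated for the post-intervention measures only, so the 33% is not the plan's own figure. With a constant 0.7, the extra loss at week 12 disappears. The article also claims over 90% power for lipid mediators, cytokines and PMN activation on medium to large pilot effects, which softens the consequence for those outcomes. All of this stands.

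Finally, the Background links area and duration to healing time only. Nothing in the article supports putting them in every biomarker or QoL model.

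**Conclusion.** The point holds as one of precision and prespecification. For outcomes measured at week 0, the analysis as stated is less precise than baseline adjustment whenever r is below 1. The variance penalty that adjustment would remove is 15% at r = 0.7, and up to 33% at week 12 if AR(1) 0.7 is assumed to extend to week 0. The age stratum is not fixed in the models; its own contribution is probably small. Ulcer area and duration are not in the covariate list, and what they would add to the wound analysis depends on an R² that the article does not give.

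Three stronger inferences should be resisted. The treatment estimates are not biased by this, because allocation is randomised. The sample size of 248 is not wrong on this account, since it reproduces without any covariate gain. And the article does not say that covariates will be picked from the baseline t tests and Chi-square tests, which it describes only as balance checks. The open wording makes it worth ruling that out, no more.

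**What to change.** - **Outcomes measured at week 0** (PMN activation, lipid mediators, cytokines, gene expression, pain, QoL): include the baseline value as a covariate, or keep week 0 in the response vector and constrain the week-0 means to be equal across arms.
- **All models:** include the age stratum used for randomisation.
- **Wound-healing models:** prespecify baseline ulcer area (log scale) and ulcer duration.
- **Selection:** state that these terms are fixed in advance and are not chosen from the baseline balance tests.

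The cost is wording only. Area is measured at visit 1, duration has to be known to establish eligibility, and age stratum is recorded at randomisation. The Trial status section reports nine participants enrolled, so at that stage the terms could be fixed well before any outcome comparison.

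### Bonferroni, the one multiplicity method named for the week 4, 8 and 12 contrasts, is valid but needlessly conservative for testing; Holm's step-down version gains power at the same family-wise error

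*Protocol article*

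**What the plan says.** The Statistical analysis section derives, from each mixed model, the between-group contrast in change from baseline at each follow-up visit. It then states: "Multiple comparison adjustment (e.g., Bonferroni adjustment) will be applied to these between-group contrasts to avoid inflated type I error".

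The Sample size section is firmer: "Our power analysis also applied Bonferroni method to adjust for three comparisons of primary interest". It lists them as "4-week vs. baseline, 8-week vs. baseline, and 12-week vs. baseline". It assumes "a first-order autoregressive covariance structure among the three post-intervention repeated measures", with a within-subject correlation of 0.7 and 20% attrition. Its conclusion is that "a total of 248 participants (124 per group) are needed to have 80% power to detect an effect size of 0.4", and it describes that effect as "an average of 16% between-group difference in percent wound area reduction with a common standard deviation of 0.4". On the error rate: "A two-sided significance level of 0.05 was used for all power analyses".

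The two sections agree with each other. Bonferroni is definite in the sizing and illustrative in the analysis.

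**The concern.** Single-step Bonferroni holds every contrast to 0.05/3, whatever the other contrasts show and however strongly they are correlated. The sizing model makes the three visit contrasts correlate at 0.7, 0.7 and 0.49, so the plan assumes marked dependence and names a procedure that ignores it. Holm's procedure tests the largest contrast at 0.05/3, the next at 0.05/2 and the last at 0.05, stopping at the first failure. It needs no assumption about correlation and cannot reject less than Bonferroni.

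What is at stake is avoidable loss of power when a true effect is present at more than one visit. The adjustment is promised for every mixed-model outcome with several follow-up visits, including wound area reduction and PMN activation, so the loss can recur across models.

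**Working it through.** **Inputs (Sample size section).** Two-sided 0.05; three contrasts; 124 per arm; 20% attrition, so 124 × 0.8 ≈ 99 evaluable per arm; effect 0.16/0.4 = 0.4; AR(1) with correlation 0.7, giving 0.7, 0.7 and 0.7² = 0.49. The document gives one average effect. Applying 0.4 at every visit is an assumption, varied below.

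**Reproducing the plan's figure.** The variance factor for the mean of three AR(1) measures is [3 + 2(0.7 + 0.7 + 0.49)]/9 = 0.7533. At 0.05/3 two-sided and 80% power, n per arm = 2(2.394 + 0.842)² × 0.7533/0.4² ≈ 98.6, so 99. Then 99/0.8 = 123.75, so 124 per arm and 248 in total. The stated size therefore reproduces with Bonferroni for the effect averaged over the three visits. (A single visit at unadjusted 0.05 also gives 99, then 124.)

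**Power per visit with Bonferroni.** The expected z is 0.4 × √(99/2) = 2.814. Power = Φ(2.814 − 2.394) = Φ(0.420) ≈ 66%.

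**Bonferroni against Holm.** Simulation of trivariate normal contrasts (2,000,000 draws), critical |z| 2.394 for Bonferroni and 2.394/2.241/1.960 for Holm, 99 per arm, AR(1) 0.7:

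| Effect at weeks 4/8/12 | Bonferroni, power per visit | Holm, power per visit | At least one visit (both methods) | All three: Bonferroni → Holm |
|---|---|---|---|---|
| 0.4/0.4/0.4 | 66.4/66.3/66.3% | 73.8/73.1/73.8% | 84.7% | 46.3 → 62.7% |
| 0.2/0.3/0.4 | 16.2/38.9/66.3% | 25.4/44.8/67.9% | 70.4% | 12.9 → 23.7% |
| 0.133/0.267/0.4 | 7.3/30.3/66.3% | 13.5/35.6/67.1% | 68.4% | 6.0 → 12.8% |
| 0/0/0.4 | week 12: 66.3% | week 12: 66.3% | 67.6% | not relevant |

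The week-12 gain is 7.5 points in the first row, then 1.6, 0.8 and about 0.

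**Family-wise error.** With no effect at any visit, Bonferroni rejects at least once in 4.1% of trials. Holm's first step is the same test, so its figure is also 4.1%.

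**Sensitivity.** With all correlations 0.7, Holm gives about 73% per visit. With change-from-baseline contrasts under AR(1) over four visits, it gives 73-74%. With no attrition (124 per arm), power per visit goes from 77.5% to 83-84%.

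**Further step.** Step-down max-t, which uses the correlation, has a first critical value of 2.31 and reaches 75% per visit in the equal-effect case, against 73-74% for Holm. When the effect builds up, it gains 3-4 points at week 12.

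**How often Holm and Bonferroni intervals disagree (equal effects).** The gap in all-three probability is a lower bound on trials with at least one Holm rejection whose Bonferroni interval includes zero: 62.7 − 46.3 = 16.4%. The summed per-visit gains are an upper bound: 7.4 + 6.8 + 7.5 = 21.7%.

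**The case against.** **The method is not fixed.** The wording gives Bonferroni as an example, so Holm is already permitted, and a statistical analysis plan not shown may settle the matter. This stands: it would be wrong to say that the analysis is committed to Bonferroni. But it is the only method named and the one used for sizing, so it is the natural default.

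**Nothing is wrong with Bonferroni.** Also true. It keeps the family-wise error at or below 5% under any correlation. A reader might infer an error or a contradiction between the two sections; there is none.

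**The gain may be small where it counts.** A reader might take 7 points as the gain at every visit in any circumstances. It is the equal-effect case only, and at week 12 the gain can be negligible. A reader might also carry it over to the biomarkers, but the Sample size section claims over 90% power and medium to large effects for those. At a standardised effect of 0.6 the gain is about 2 points.

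**Holm does not recover the unused error.** Correct. A reader might expect a step-down test to turn 4.1% into 5%. Only a correlation-based method does that, and it relies on an estimated covariance that must be carried through the planned multiple imputation and pattern-mixture analyses. That is why Holm, not max-t, is the recommendation.

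**It is not free.** Bonferroni tests and intervals always agree; Holm tests and Bonferroni intervals do not. This cost is real, though it affects presentation and not error control.

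**Conclusion.** The point holds as a modest efficiency improvement. For testing, Bonferroni has no advantage over Holm in error control, and Holm is never less powerful. Under the plan's assumptions with an effect of 0.4 at every visit, the gain is about 7 points per visit and about 16 points in the chance that all three visits are significant. It depends on true effects at more than one visit and shrinks at week 12 if the effect accrues. The chance of detecting an effect at some visit is unchanged. The plan's error control is sound as written, and its total of 248 is not challenged here. The change should not be presented as restoring 80% power for each contrast: with 99 per arm, Holm reaches 73-74%.

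**What to change.** In the Statistical analysis section, replace the Bonferroni example with *Holm step-down adjustment over the week 4, 8 and 12 contrasts*, and state that significance is decided by Holm. Keep Bonferroni-adjusted simultaneous confidence intervals, with a note that a Holm rejection may accompany an interval that includes zero. Single-step max-t intervals are an alternative and are about 3.5% narrower. Because their critical value (2.31) lies below Holm's first (2.394), disagreement with the Holm tests could then run in either direction. Step-down max-t testing is an optional refinement if the covariance can be handled across the missing-data analyses.

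The Sample size section can stay, since sizing with Bonferroni is conservative for a Holm analysis. The cost is one sentence and a note on intervals, with standard software and no extra participants. The article reports nine participants enrolled, so the change can be made well before any analysis.

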At the end of this trial, we expect to know the extent that EPA + DHA therapy and the proposed mediating factors reduce PMN activation, expedite CVLU healing, and prevent recurrence. We expect to know more about the mechanisms of action of EPA + DHA therapy and its subsequent impact on ulcer pain and QoL. This knowledge will propel us toward our long-term goal *–* to help prevent or facilitate healing of CVLUs in aging and thereby improve QoL. After this study, next steps may include (1) a pragmatic trial to test EPA + DHA therapy in the everyday clinical setting to maximize generalizability, assess cost effectiveness, and determine the feasibility of using a point-of-care test [55] that can measure protease levels in CVLU fluid within minutes, (2) determining the extent that EPA + DHA therapy prevents CVLUs in people with known venous disease, and (3) determining the extent that genetic factors affect EPA + DHA metabolism. We predict that EPA + DHA oral therapy added to standard topical care will greatly improve CVLU healing outcomes and as such, reduce the substantial emotional and financial burdens caused by these serious wounds in aging (Additional file 1).

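### The recurrence comparison will have about 40–50 people: too few for reliable covariate-adjusted logistic regression if recurrence is uncommon, or for claims beyond preliminary efficacy

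*Protocol article*

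**What the plan says.** Protocol article, Secondary outcome measures: "CVLU recurrence will be assessed in two subgroups derived from the EPA + DHA group". Those healed by week 12 who agree to continue are re-randomised 1:1 to EPA + DHA or placebo and seen once, three months later. The section calls the aim preliminary efficacy.

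Statistical analysis: "Logistic regression modeling will be used to analyze wound recurrence". The target is the between-group difference in recurrence risk, "adjusting for potential covariates and multiple comparison". The section adds that sex and its interaction with treatment will be examined in the regression models. It sets no limit on covariates for this outcome and names no method for sparse data. Covariates lists at least six kinds of candidate variable (age, sex, tobacco use, comorbidities, stress, medications), then diet, debridement, adjunct therapies and dressing type.

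Sample size covers percent wound area reduction, lipid mediators, cytokines and PMN activation. It gives no size, event count or power for recurrence.

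On what will be learned, the Background expects to close a knowledge gap that includes preventing recurrence. The Discussion makes the effect on recurrence a main goal and expects to know the extent to which therapy and "the proposed mediating factors reduce PMN activation, expedite CVLU healing, and prevent recurrence".

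**The concern.** The recurrence comparison uses a fraction of one arm. With few events, maximum-likelihood logistic regression can break down: if a subgroup has no events, or the covariates separate events from non-events, the treatment odds ratio has no finite estimate. When a fit does exist, odds ratios from a model with many terms and few events lie on average too far from no effect. The subgroups are re-randomised, so a long covariate list is not needed to remove confounding by design, yet it adds to this fragility. Separately, a comparison of this size gives a wide interval, and everyone in it healed on EPA + DHA. It can therefore inform continuing versus stopping in that group, which is narrower than whether the therapy prevents recurrence.

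**Working it through.** **The plan's own figure.** "a total of 248 participants (124 per group) are needed to have 80% power to detect an effect size of 0.4". Inputs from Sample size: difference 0.16, SD 0.4, two-sided 0.05 with Bonferroni for three comparisons, three AR(1) measures with correlation 0.7, 20% attrition.
- Variance factor for the average of three measures: (3 + 2(2 × 0.7 + 0.49))/9 = 0.753.
- n per arm = 130.9 × 0.753 = 98.6, so 99. Then 99/0.8 = 124 per arm, 248 in total. The figure reproduces, for wound area reduction.

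**Size of the recurrence comparison.** The Background says "nearly 60% of CVLUs remain unhealed after 12 weeks of compression therapy", so about 40% are healed.
- 124 × 0.4 = 49.6; after attrition, 99 × 0.4 = 39.6. With full consent that is 20–25 per subgroup.
- Low end, 70% consent (assumed): 99 × 0.4 × 0.7 = 27.7. High end, 60% healing (assumed): 124 × 0.6 = 74.4.

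**Events and power.** The 3-month recurrence rate is not in the document. Assumed placebo-subgroup rates are halved by treatment; tests are two-sided at 0.05.

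| Placebo-subgroup rate | Events, N = 40 | Power, N = 40 | Events, N = 50 | Power, N = 50 | Needed per subgroup for 80% |
|---|---|---|---|---|---|
| 10% | 3 | 9% | 3.8 | 10% | 435 |
| 20% | 6 | 14% | 7.5 | 16% | 199 |
| 30% | 9 | 20% | 11 | 24% | 121 |
| 40% | 12 | 28% | 15 | 33% | 82 |
| 50% | 15 | 37% | 19 | 45% | 58 |

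At N = 74 and a 50% rate, power is still only 61%.

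**Precision.** Half-width = 1.96 × sqrt(p1q1/n + p0q0/n). For 20% v 10% at n = 25: 1.96 × sqrt(0.25/25) = 0.196. For 40% v 20% at n = 20: 1.96 × sqrt(0.40/20) = 0.277. So about ±20 to 28 points.

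**Non-finite fits.** With no covariates, 20 per subgroup and 20% v 10%, the chance of a zero-event subgroup is 1 − (1 − 0.9^20)(1 − 0.8^20) = 1 − 0.878 × 0.988 = 13%. Simulation (1,500 trials per setting, covariate odds ratios 1.5) gives these shares with no finite estimate:

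| Placebo-subgroup rate | N = 40, no covariates | N = 40, 4–6 covariates | N = 50, 4–6 covariates |
|---|---|---|---|
| 10% | 43% | 59–68% | 47–53% |
| 20% | 13% | 24–29% | 13–15% |
| 30% | 5% | 8–10% | about 4% |
| 40% | 2% | 2–4% | about 1% |

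A separate simulation at N = 40, with six covariates that have no true effect, gave 35%, 10% and 3% at rates of 20%, 30% and 40%.

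**Exaggeration among finite fits.** In that separate simulation the mean log odds ratio was −0.99, −1.25 and −1.36 against true values −0.81, −0.89 and −0.98, that is 22%, 40% and 39% too large. Firth-penalised fits averaged −0.79, −0.94 and −1.02. With 0–2 covariates at rates of 20–30%, ordinary fits were within about 0.15 of the truth.

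**Sex-by-treatment term.** These simulations did not include it. With an even sex split (assumed) there are 10 people per cell. At 20% v 10% in both sexes, the chance that at least one of the four cells has no events is 1 − (1 − 0.9^10)² × (1 − 0.8^10)² = 1 − 0.424 × 0.797 = 66%.

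**The case against.** - **Covariates.** The plan never commits to six covariates for recurrence. It speaks of potential ones, and the list is gathered for all outcomes. An SAP that is not shown may fix a short set. This stands: the exaggeration applies to a many-covariate model, and the stated text also permits a sparse one.
- **Recurrence rate.** The article gives no 3-month figure. It says ulcers usually recur, without a time frame. A reader might infer that the planned method will fail or will overstate the benefit. The documents do not support that: it is a conditional risk, and failed fits are rare at 40% or more.
- **Size.** The 40% healed is a compression-therapy figure. The same Background paragraph gives a 12-week median healing time for uncomplicated ulcers, and an effective treatment would heal more. Incomplete consent works the other way. Hence the range of 28–74.
- **Effect measure.** The plan already targets a difference in risks, while the bias evidence concerns odds ratios. The excess of 0.18–0.38 in the log odds ratio is also only about 0.2–0.5 of its standard error (about 0.93, 0.79 and 0.72 at 20 per subgroup). So imprecision is the larger problem.
- **Multiplicity.** A reader might also object to the promised multiplicity adjustment. For a single contrast a Bonferroni correction changes nothing, so no point is made of it.
- **Wording.** Recurrence is a secondary endpoint, already labelled preliminary, and the Discussion text is an expectation and not a decision rule. This limits the weight of the inconsistency but does not remove it.

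**Conclusion.** The point holds as a conditional risk and a mismatch of claims. The size of about 40–50 follows from the article's figures if consent is full and healing is near 40%. At assumed placebo-subgroup rates of 10–30%, an ordinary logistic model with 4–6 covariates fails to give a finite estimate in about 8–68% of trials at N = 40. The risk of failure is small at 40% or more. Few covariates remove most of the exaggeration, but at rates of 10–20% even an unadjusted fit fails in 43% and 13% of trials. The limit on the conclusion depends less on these assumptions: power to detect a halving stays at about 9–45% for N = 40–50 across all rates tried, so the stronger wording in the Background and Discussion goes beyond the label under Secondary outcome measures. This affects a secondary endpoint only.

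**What to change.** In Statistical analysis, specify a Firth-penalised or exact analysis of recurrence, adjusted at most for the randomisation age stratum. Report the already planned risk difference with a score-based 95% CI as the main result. Treat the sex-by-treatment comparison as descriptive for this outcome. State the expected size of the comparison, about 40–50, and its precision. In the Background and Discussion, describe recurrence as a preliminary estimate of continuing versus stopping EPA + DHA among people who healed on it, in line with Secondary outcome measures.

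The cost is wording and a standard software option. The downside is a more modest stated conclusion and less covariate adjustment.
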